#### Process evaluation

REAIM (reach, effectiveness, adoption, implementation and maintenance) framework for the process evaluation will be used for mWellcare trial.^25^ This would entail a combination of qualitative (observations, interviews, focus group discussions) and quantitative (open-ended and close-ended questionnaires) assessment.

Fidelity will be assessed through logs of training, indicators from OSSO checklist and data captured through mWellcare system. Besides reports of monitoring visits by experts will form a part of the assessment.

#### Economic evaluation

To help inform potential financing and adoption of the mWellcare intervention, compared with enhanced care (control), we will estimate the value for different stakeholders: patients (mean annual health expenditures in each arm), healthcare providers (incremental costs to deliver the intervention and cost-effectiveness: eg, incremental cost to prevent one CVD event) and society (cost-utility: eg, cost per quality-adjusted life years gained).

We will collect patient-level healthcare utilisation and medical costs data incurred during the trial regarding outpatient visits, diagnostic services, medications, hospitalisations and lost productivity.^26^ We will identify intervention costs from the non-communicable disease clinic and study expenditures (eg, costs related to accessing the mWellcare system, and sending the regular SMS updates, training costs, labour costs for nurses, physician’s time cost and overhead costs minus costs attributable only to research activities (eg, annual study visit)). We will compute the incremental costs of intervention (implementation, adverse effects, medical care associated) compared with control. For effectiveness measures, we will use between-group differences in SBP and HbA1c reductions. Utility data will be collected using the EQ5D Visual Analogue Scale.

If the primary clinical outcomes (SBP and HbA1c) are shown to differ substantially, a full economic evaluation of the lifetime costs, benefits and cost-effectiveness (in life years gained and quality-adjusted life years gained) of switching from usual care to mWellcare intervention using decision models will be performed.^27^ Uncertainty around incremental cost-effectiveness ratio will be estimated using non-parametric bootstrap methods. To inform societal perspective, we will calculate an incremental cost-utility ratio($\frac{costs_{intervention}-costs_{control}}{utility_{intervention}-utility_{control}}$).^28^ To standardise for the time value of money, we will use a 3% annual discount rate. Costs will be expressed in rupees and US$ (2016 value). We will conduct sensitivity analyses where discount rates, intervention costs, effectiveness and other model parameters will be varied to estimate cost-utility under different scenarios.^29^ We will also generate cost-effectiveness acceptability curve to demonstrate the probability of cost-effectiveness of the intervention at a range of willingness to pay threshold values. If no significant difference is found for the primary clinical outcomes, a cost-minimisation analysis will be performed.

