### Data collection, management and analysis

#### Baseline assessment

After consent, the nurse in both arms collected baseline data for the following parameters using a tablet computer: age, gender, marital status, occupation, alcohol use, smoking behaviour, health-related quality of life measured using EuroQol five dimensions questionnaire (EQ-5D), height, weight, blood pressure and blood sugar. Consented participants were asked to return on a scheduled day for blood sample collection for HbA1c and total cholesterol.

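### The article names the EQ-5D visual analogue scale as the source of utilities, but a cost-utility ratio built on that rating is not a cost per QALY

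*Protocol article*

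**What the plan says.** All the relevant text is in the protocol article.

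- **Utility source** (Economic evaluation): "Utility data will be collected using the EQ5D Visual Analogue Scale".
- **Use of the utility** (same section): the societal measure is given as "society (cost-utility: eg, cost per quality-adjusted life years gained"). Later the section says "To inform societal perspective, we will calculate an incremental cost-utility ratio", and the formula printed there divides the difference in costs between arms by the difference in utility.
- **Lifetime model** (same section): if the primary outcomes differ substantially, a full evaluation is planned that covers "cost-effectiveness (in life years gained and quality-adjusted life years gained) of switching from usual care to mWellcare intervention using decision models". A cost-effectiveness acceptability curve is also planned. If the primary outcomes show no significant difference, a cost-minimisation analysis is done instead.
- **Quality-of-life instrument** (Baseline assessment): the nurse records "health-related quality of life measured using EuroQol five dimensions questionnaire (EQ-5D"). The Endline assessment section names no instruments.

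**The concern.** The EQ-5D has two parts. The five-dimension responses describe a health state, which a preference-based value set converts into an index. The VAS is a separate 0 to 100 self-rating of current health, running from worst to best imaginable.

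A QALY weight has to be a preference-based value on a scale where dead is 0 and full health is 1. The VAS meets neither condition: the respondent makes no choice or trade-off, and the bottom of the scale is not dead. Time multiplied by a VAS score is therefore not a QALY.

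The article chooses the VAS explicitly. It does not merely leave the scoring unstated. A reader who followed the text would put the wrong part of the instrument into the denominator of the cost-utility ratio, and the result could not be set against a willingness-to-pay threshold per QALY. Cost-effectiveness is among the secondary objectives, and the Discussion says the findings should help decision makers allocate resources, so this output matters.

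**Working it through.** The article states no utility value, QALY total or cost-utility ratio, so there is no figure to reproduce. The check is a comparison of the text, followed by a short piece of algebra.

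**Step 1: what the ratio needs and what is supplied.** The Economic evaluation section promises a cost per QALY, which needs a preference-based weight. The only utility source it names is the VAS. Nothing in the article says that VAS scores will be transformed into utilities, or that the five-dimension responses will be scored with a value set.

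**Step 2: whether another section supplies the utility.** The Baseline assessment section lists the EQ-5D questionnaire as a quality-of-life measure and does not link it to utilities. The Endline assessment section lists no instruments. The article therefore does not show that five-dimension responses will exist at 12 months.

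**Step 3: which results are reached.**

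| Planned result | Does it rest on the VAS? |
|---|---|
| Cost-utility ratio from trial data | Yes: utility is the denominator and the VAS is the only utility named |
| QALYs in the lifetime model | Not stated: the model's utility inputs are not given |
| Acceptability curve | Not stated: the unit of the threshold is not given |
| Cost against differences in SBP and HbA1c, or per CVD event prevented | No: no utility is used |
| Cost-minimisation analysis | No: no utility is used |

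**Step 4: how the ratio responds.** Let ΔC be the cost difference and ΔU the utility difference, so that the ratio is ΔC / ΔU. Write the VAS difference (rescaled to 0 to 1) as k times the index difference:

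ratio with VAS = ΔC / (k × ΔU index) = (1/k) × ratio with index

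The documents give no value for k. The values below are assumptions that only show how the formula behaves:

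| Assumed k | Ratio with VAS, as a multiple of the index-based ratio |
|---|---|
| 0.5 | 1/0.5 = 2.00 |
| 0.75 | 1/0.75 = 1.33 |
| 1 | 1/1 = 1.00 |
| 1.25 | 1/1.25 = 0.80 |
| 1.5 | 1/1.5 = 0.67 |
| 2 | 1/2 = 0.50 |

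The two ratios agree only at k = 1. Nothing in the article supports k = 1 or any other value, so the table says nothing about the likely error in this trial.

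**The case against.** The strongest reply is that the sentence is loose shorthand. It says how utility data are collected, not how they are scored. The Baseline assessment section names the full questionnaire, and a condensed article may leave the value set and the construction of QALYs to a fuller document. Part of this stands: an unnamed value set would be no finding, and the intended analysis may be sound. But the sentence names the VAS component specifically. If the whole instrument was meant, the sentence is still wrong and must be reconciled with the Baseline assessment section.

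A second reply is that the consequence may never arise. This also stands in part. The lifetime evaluation is conditional on a substantial difference in the primary outcomes, and the cost-minimisation branch uses no utility. The effectiveness measures named in the section, SBP and HbA1c, need none either.

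Two stronger readings are tempting, and the documents do not support them:

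- A reader might infer that the lifetime QALYs and the acceptability curve must also be invalid. The article does not say where the model takes its utilities or in what unit the threshold is expressed.
- A reader might infer that the five-dimension responses needed for an index are already in hand, so that only rescoring is required. The article places the EQ-5D at baseline only.

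**Conclusion.** The point holds in a limited form. As written, the article takes utilities from a rating that is not a preference-based utility, and the cost-utility ratio computed from trial data would not be a cost per QALY. The error is of unknown size and direction, because the documents contain no utility or cost figures. The factor of 2.00 to 0.50 follows purely from the assumed range of k from 0.5 to 2.

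The conclusion rests on reading the utility sentence as it stands, and on the absence of any other named utility source. The lifetime-model QALYs and the acceptability curve are affected only if they draw on the same utilities. The estimates for SBP, HbA1c and the other clinical outcomes are not affected. The sentence should be corrected, but the trial's main conclusion does not depend on it.

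**What to change.** Replace the utility sentence in the Economic evaluation section with:

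> Utilities will be index values from the EQ-5D five-dimension responses at baseline and 12 months, scored with one published value set named before unblinding; the VAS is reported descriptively.

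Confirm that the five-dimension items are part of the endline assessment, and add them if they are not. The article describes the endline assessment in the future tense, so this was still possible when it was written.

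The cost is small. A value set has to be chosen and justified in advance, and a few questionnaire items may have to be added at endline. Neither the design nor the clinical analysis changes.

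### The only method named for uncertainty in the cost-effectiveness ratio is a bootstrap, which cannot carry uncertainty in the lifetime model's external inputs

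*Protocol article*

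**What the plan says.** All of the relevant text is in the Economic evaluation section of the protocol article.

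- **Trial data.** The section states "We will collect patient-level healthcare utilisation and medical costs data incurred during the trial", and for effects "For effectiveness measures, we will use between-group differences in SBP and HbA1c reductions". Utilities are also collected in the trial. Follow-up is 12 months (Intervention; Participant timeline).
- **Lifetime model.** If SBP and HbA1c differ substantially, a full evaluation of lifetime costs and benefits "of switching from usual care to mWellcare intervention using decision models will be performed", in life years and QALYs.
- **Uncertainty in the ratio.** The next sentence is "Uncertainty around incremental cost-effectiveness ratio will be estimated using non-parametric bootstrap methods". The resampling unit and the number of replicates are not given.
- **Model parameters.** In sensitivity analyses, "discount rates, intervention costs, effectiveness and other model parameters will be varied to estimate cost-utility under different scenarios". No distributions are mentioned.
- **Acceptability curve.** "We will also generate cost-effectiveness acceptability curve to demonstrate the probability of cost-effectiveness of the intervention at a range of willingness to pay threshold values". The text does not say which replicates or draws the curve is built from.

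**The concern.** A non-parametric bootstrap resamples observed records, so it can express only the sampling error in what was recorded. For a 12-month ratio built from trial costs and trial effects, that is appropriate. A lifetime ratio also depends on quantities for which the trial holds no records. Scenario analyses show how the point estimate moves when such an input is changed, but they add nothing to the interval or to a stated probability.

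An analyst who follows the section literally would therefore report a lifetime interval that reflects trial sampling error and treats the external inputs as known. The section says the evaluation is meant to inform financing and adoption, and the Discussion points to scale-up decisions. Overstated certainty would reach the readers for whom the analysis is done.

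**Working it through.** **1. Is there a figure to reproduce?** No. The document gives no cost-effectiveness ratio, standard error, replicate count or acceptability probability. The check is therefore of mechanism and direction, with an illustration under stated assumptions.

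**2. Which inputs can the bootstrap reach?**

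| Input to the lifetime ratio | Recorded in the 12-month trial? | Route into the interval as written |
|---|---|---|
| Patient-level costs during the trial | Yes | Bootstrap |
| SBP and HbA1c differences at 12 months | Yes | Bootstrap |
| Utilities during the trial | Yes | Bootstrap |
| Conversion of SBP/HbA1c differences to life years | No | None stated |
| Costs and utilities after month 12 | No | None stated |
| Persistence of effect after month 12 | No | None stated |

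**3. Direction and possible size.** Take incremental net benefit as approximately normal. Suppose the bootstrap alone gives probability p of cost-effectiveness. Add independent model-parameter variance equal to k times the bootstrap variance, and leave the mean unchanged. Then

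- the interval for net benefit widens by a factor √(1+k);
- the probability becomes Φ(z(p)/√(1+k)).

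For p = 0.95, z = 1.645:

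- k = 0.25: 1.645/1.118 = 1.471, so 0.929
- k = 1: 1.645/1.414 = 1.163, so 0.878
- k = 3: 1.645/2 = 0.822, so 0.795

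| Bootstrap-only probability | k = 0.25 | k = 1 | k = 3 |
|---|---|---|---|
| 0.80 | 0.774 | 0.724 | 0.663 |
| 0.90 | 0.874 | 0.818 | 0.739 |
| 0.95 | 0.929 | 0.878 | 0.795 |
| 0.975 | 0.960 | 0.917 | 0.836 |

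The values of k are assumptions; none comes from the document.

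**4. What the plan's figures do fix.** Sample size calculation gives SD 15 mm Hg, ICC 0.05, 40 hypertensive participants per cluster, 40 clusters (20 per arm) and 20% loss. That leaves 40 × 0.8 = 32 analysed per cluster. The standard error of the SBP difference is √(2 × 15² × (1 + 31 × 0.05)/(20 × 32)) = 1.34 mm Hg, and 1.34/4 = 33% of the 4 mm Hg target. This describes part of the trial side only. It does not give k, because the document has neither the sampling error of costs nor any uncertainty for the external inputs.

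**5. Why persistence is not a minor input.** At the stated 3% rate, discounted years of effect over T years are (1 − 1.03^−T)/ln 1.03. This gives 0.99 for T = 1, and 8.7, 15.1 and 19.9 for T = 10, 20 and 30. The durations are assumed; the document gives none. The planned scenarios could display this spread. The bootstrap could not, so the spread would not enter the interval.

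**The case against.** The strongest reply is that the bootstrap sentence speaks of a cost-effectiveness ratio without calling it lifetime. The section lists all the ingredients of a within-trial ratio, for which the bootstrap is suitable. It then attaches parameter variation to cost-utility. One can therefore read it as a bootstrap for trial-based ratios and parameter variation for the model. The article is also condensed: distributions and joint draws may stand in a fuller document that is not shown, and the lifetime model is conditional and secondary.

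Much of this stands. In particular, a reader might infer that the planned acceptability curve leaves out the model's uncertainty and is too steep. The document does not support that as a fact, because it never says what the curve is built from. Nor does it say that parameters are varied one at a time or held fixed inside the bootstrap, and probabilistic draws are not ruled out. Any translation into probabilities rests on assumed variances. One that scales up the uncertainty in effect alone would also ignore sampling error in costs, and so overstate the change.

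The reply does not remove the point. The bootstrap sentence directly follows the lifetime model and is the only statement on uncertainty in the ratio. The difficulty is that a method is named which falls short for the quantity just described, so it is more than an omitted detail. Under the more favourable reading, the lifetime ratio has no stated uncertainty method other than scenarios.

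**Conclusion.** The point holds in this form: as written, uncertainty in external model inputs has no stated route into the lifetime ratio's interval, which would therefore generally overstate certainty. The acceptability curve would do the same if it uses the bootstrap replicates alone, and that condition is not settled by the text.

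The size cannot be derived from the document. With k between 0.25 and 3, a bootstrap-only 95% becomes about 93% to 80%, and the net-benefit interval should be 1.12 to 2 times as wide. This rests on approximate normality, independence of the two sources and an unchanged mean net benefit. In a non-linear model the curve may shift as well as flatten. The matter is confined to a conditional secondary economic analysis and has no bearing on the primary clinical comparison.

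**What to change.** In the economic analysis plan, separate the two ratios:

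- **Within-trial 12-month ratio:** keep the non-parametric bootstrap alone.
- **Lifetime ratio and its acceptability curve:** use a probabilistic sensitivity analysis. Each draw takes trial costs and effects jointly (from bootstrap replicates, or from the fitted model's estimates and covariance). The same draw samples the external parameters, including persistence of effect after month 12, from stated distributions. Compute both the interval and the curve from these draws, and say so.
- **Scenarios:** keep them for structural choices such as the discount rate.

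The cost is wording and some modelling time; no new trial data are needed. The downside is a wider interval and a flatter curve.

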#### Data monitoring

A four-member DSMB has been established. DSMB members are independent from sponsor and have no conflict of interest. The board members include experts in biostatistics, ethics and cardiovascular disease management. Based on observed beneficial or observed effect, DSMB will make recommendation to the Research Steering Group (RSG) in relation to the conduct of the trial (continue, change or terminate). The RSG takes responsibility for the design, conduct and analysis of the clinical trial. RSG is a multidisciplinary group who, collectively, has the scientific, medical and clinical trial management experience to conduct and evaluate the trial. In addition, a Research Management Committee) consisting of principal investigators, co-investigators, project manager and other team members have been formed to monitor progress of the study.

#### Serious adverse events

Occurrence of serious adverse events that include severe hypoglycaemia, CVD events, diabetes-related gangrene or amputation, end-stage renal disease and death is being monitored. Information about the occurrence of any adverse event is sought at all scheduled visits, and outside of scheduled visits by participant self‐report and tracking of non‐study-related visits. All events reported in the study will be duly notified to the overviewing ethics committees and DSMB in the annual progress report.

## Discussion

mWellcare is the first study in India, assessing the effectiveness of mHealth technology for integrated management of hypertension and diabetes at primary care level in a public health setting. Few trials have evaluated the impact of DSS on managing patients with hypertension and diabetes. A recent cluster randomised trial in Andhra Pradesh, India, which evaluated the use of DSS in hypertension management, demonstrated significant reduction in SBP among patient in primary healthcare facilities.^21^ However, this trial focused only on hypertension while the other cardiometabolic risk factors were not covered. The recently published results of Cardiometabolic Risk Reduction in South Asia (CARRS) Diabetes Trial shows significant improvement in diabetes care targets and cardiometabolic risk reduction among patients who underwent multicomponent quality improvement intervention comprising non-physician care coordinators and decision support electronic health records.^30^ However, the findings of CARRS trial are confined to urban specialist care settings.

mWellcare trial with its cluster randomised design will extend the evidence on impact of mHealth intervention on patient’s CVD outcomes at primary care level. It will provide evidence on the use of nurse for patient assessment and long-term follow-up using the mWellcare system thereby shifting/sharing some of the patient management tasks from physicians. It is also designed to provide decision support to physician for standardised and integrated management of hypertension and diabetes along with comorbid condition such as depression and alcohol use disorder.

The mWellcare intervention is being implemented in the real-world scenario aimed at using the existing human resource (as the nurse appointed at the outpatient clinics through the NPCDCS). The trial also incorporates cost-effectiveness analysis of the intervention. All these factors would be helpful in informing decision makers in allocating resources and scaling up the intervention based on the trial findings.

There are a few limitations for this study. The effectiveness of the trial will also depend on the availability of drugs, recommended by the decision support system, at the CHCs. Drugs are supplied by the state government and there are variations in availability across the state and districts, although such variations are likely to affect both arms equally. Another limitations is that the mWellcare system will be used only for the people who have been already diagnosed with hypertension or diabetes by the physician, and will not aid in opportunistic screening of patients coming to the CHC. This was done to keep both intervention and control arms at par. In case the intervention is scaled up, a screening module can be added to the mWellcare system.

### Conclusion

The mWellcare trial will provide evidence on effectiveness of the nurse-based mHealth intervention for integrated management of hypertension and diabetes at primary care level in India. Results from the trial will have direct policy relevance in adopting mHealth solution for managing CVDs at primary care level in India.

## Ethics and dissemination

mWellcare trial protocol and study documents have been approved by the Institutional Ethics Committee at PHFI and London School of Hygiene and Tropical Medicine. All information collected as part of this study will be kept strictly confidential. Personal identifiers will be removed before transferring data for analysis. Participant’s identity will be anonymous and postanalysis of the data, the tapes and transcripts will be destroyed. Participant’s name or identity will not be revealed in any of the publications arising from this research.

Findings from this study will be submitted for publication in peer-reviewed journals. The study results will be shared with health professionals (primary care providers), local government and decision makers as brief policy notes. The study investigators will also disseminate findings through professional conferences targeting primary and secondary care physicians, research community and public health policymakers more widely. The results of this study will provide policy-relevant recommendations for the uptake of mHealth interventions in the management of hypertension and diabetes in India.

At the end of the study, the investigators will form a Publication, Presentation and Ancillary Studies (PP&A) subcommittee, which will develop a suitable policy protecting the rights of involved organisations regarding ownership of study materials and data. The full editorial control will reside with the PP&A committee. All investigators will be given access to the cleaned data sets.
